### Data monitoring

The study was considered to involve no more than minimal risk to subjects, so the Institutional Review Board of the Second Affiliated Hospital of Xinxiang Medical University determined that a data monitoring committee was not required.

### Harms

To assess the safety and potential adverse effects of tDCS, this study will systematically analyze both serious and non-serious adverse events. Following each tDCS session, all participants will be required to complete the tDCS Adverse Events Questionnaire. Commonly reported side effects include sensations of tingling, mild erythema, itching, and discomfort at the site of stimulation. Participants will evaluate their adverse experiences on a scale ranging from 0 to 5. All adverse events will be recorded in the case report form (CRF). The tDCS device will be administered by a therapist with specialized training and experience in its application. Consequently, it is anticipated that participants will not encounter any significant health risks or adverse events. In the event that a serious adverse event does occur, the participant will be withdrawn from the trial, and the incident will be reported to the ethics committee.

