### Eligibility criteria

Participants will be assessed based on the inclusion and exclusion criteria detailed in **Table 1**. All patients routinely undergo the Drug Abuse Screening Test (DAST-10) and the Alcohol Use Disorders Identification Test (AUDIT) at admission, which are standard procedures at our hospital. During the enrollment, we will assess drug and alcohol abuse by reviewing the standardized test results and medical records of patients at admission. Severe drug and alcohol dependence, defined as a score of ≥3 on the DAST-10 (28) or ≥8 on the AUDIT (29) will be excluded from the study. The study will be discontinued under the following conditions: (1) the emergence of urgent medical issues; (2) the occurrence of serious adverse events and side effects; or (3) the participant or their family members express unwillingness to continue participation in the trial. Participants had been on a stable dose of antipsychotic medication for a minimum of two weeks, before the trial began. These medication doses remained unchanged throughout the study.

**Table 1 T1:** Inclusion and exclusion criteria.

Inclusion criteria
1. Meets the clinical diagnostic criteria for schizophrenia according to DSM-5 for the current episode.
2. Patients who achieve a stable period through oral antipsychotic drug treatment are defined by the following criteria: a score of ≤5 on the items of delusion, hallucinatory behavior, exaggeration, and suspiciousness/victimization in the Positive and Negative Symptom Scale (PANSS), and a score of ≤4 on the PANSS conceptual disorganization.
3. Currently undergoing treatment with atypical antipsychotic medications, with equivalent doses of antipsychotic drugs calculated using the defined daily dose method.
4. Han ethnicity.
5. Ages between 18-55 years.
6. Normal hearing.
Exclusion criteria
1. Presence of brain organic lesions, intellectual disability, or other physical illnesses.
2. Frequent or persistent migraines.
3. Metal in skull and pacemaker.
4. Currently having epilepsy or a family history of epilepsy and other mental illnesses.
5. Severe drug and alcohol dependence.
6. Pregnant or lactating women.
7. Currently undergoing other neurostimulation therapy or evidence-based psychotherapy.

DSM-5: Diagnostic and Statistical Manual of Mental Disorders, 5th edition; PANSS, Positive and Negative Syndrome Scale.

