### Outcomes

The study will utilize the Chinese version of the MATRICS Consensus Cognitive Battery (MCCB), which has demonstrated high efficacy in assessing cognitive function. To mitigate potential learning effects, various parallel versions of the MCCB will be employed at different assessment stages. Previous studies have demonstrated that the Chinese version of MCCB exhibits good test-retest reliability and validity, making it suitable for assessing cognitive dysfunction in patients with schizophrenia at each visit (31, 32). Cognitive function and psychotic symptoms will be assessed at baseline (T0), after 2 weeks (T1), and after 4 weeks (T2). According to the literature, intraclass correlation coefficient (ICC) will be used to assess the consistency of the assessors (33). The ICC values among assessors were 0.912, indicating the consistency was good. The procedure for the site visit is detailed in **Table 3**.

**Table 3 T3:** Time schedule of screening, interventions and assessments.

	Recruitment	Baseline	Assessments	
			After 2 weeks	After 4 weeks
Time point		T0	T1	T2
Prescreening for eligibility, consenting and clinical interview				
Recruitment				
Eligibility screening	✓			
Informed consent	✓			
Allocation	✓			
Primary outcome assessment				
MCCB		✓	✓	✓
Second outcome assessment				
BPRS		✓	✓	✓
PANSS		✓	✓	✓
CGI		✓	✓	✓
SQLS		✓	✓	✓
SDSS		✓	✓	✓
fNIRS		✓	✓	✓
GIQ		✓		

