### Statistical methods

The Shapiro-Wilk Test will be used to analyze whether the data conform to normality. If the quantitative data conform to a normal distribution, they will be expressed as the mean and standard deviation (SD); if they do not, they will be displayed as median values and interquartile range (IQR). Categorical data will be presented as counts with percentages. To evaluate differences in baseline characteristics between groups, t-tests, nonparametric tests, chi-square tests, Mann-Whitney U tests, and ANOVA will be employed appropriately. The Fisher exact test or χ² test will be used to compare adverse effects between groups.

In accordance with the CONSORT guidelines, analyses will be conducted following the intention-to-treat (ITT) principle, whereby all participants will be analyzed as originally randomized. A line graph will be utilized to depict values across different time points. To evaluate between-group and within-group differences over time for both primary and secondary outcomes, we will appropriately apply generalized linear mixed models and repeated measures ANOVA. A stepwise model selection process will be utilized to identify a parsimonious multivariable regression model. Age, gender and DDD doses of antipsychotic medications will be included as covariates in all models. The likelihood ratio test (LRT) will be utilized to assess the treatment effect by determining whether the coefficients for both the treatment and the interaction between time and treatment in the model are equal to zero. To account for multiple comparisons across multiple time points, p-values will be adjusted using the Bonferroni correction method. All statistical analyses will be conducted using SPSS 20.0. P < 0.05 is considered to be a statistically significant difference.

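### A serious adverse event takes the participant out of the trial, not only off the intervention, so later MCCB and safety assessments are lost

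*Protocol article*

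**What the plan says.** The rule is in *Harms*: "In the event that a serious adverse event does occur, the participant will be withdrawn from the trial", with a report to the ethics committee. It has no causality condition, so an unrelated serious event triggers it too.

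*Eligibility criteria* points the same way. It gives three grounds for discontinuing the study: urgent medical issues, "the occurrence of serious adverse events and side effects", and unwillingness of the participant or family to continue. A medical event and a refusal are thus handled alike. It is unclear whether the word serious also covers the side effects, and nothing below depends on that.

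Three other statements bear on the rule:

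- *Statistical methods* commits to intention-to-treat, "whereby all participants will be analyzed as originally randomized", and says of the models that "we will appropriately apply generalized linear mixed models and repeated measures ANOVA".
- *Outcomes* and Table 3 schedule the MCCB (the primary outcome is its change) at T0, T1 (2 weeks) and T2 (4 weeks), and the Adverse Reaction Scale at T1 and T2.
- *Harms* promises that "this study will systematically analyze both serious and non-serious adverse events".

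The article nowhere says that a participant withdrawn after a serious event keeps the remaining T1 or T2 visits.

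**The concern.** Stopping treatment and stopping observation are different decisions. An intention-to-treat comparison needs outcomes from patients who stopped treatment as well as from those who completed it. A rule that ends participation after a serious event removes those outcomes, and no later analysis plan can recover values that were never collected.

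The trigger occurs after randomisation and could be related both to treatment and to cognitive outcome. Groups 1 and 3 receive active current; Groups 2, 4 and 5 do not. Losses could therefore differ in comparisons such as Group 1 against music therapy alone. They are less likely to differ between Groups 1 and 3, which receive the same current. If the patients removed would have done worse, the arm that loses them looks better than it is.

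The rule also ends scheduled safety follow-up in the patients for whom it matters most, in a trial that has no data monitoring committee.

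**Working it through.** **1. The plan's own figures.** *Sample size calculation* gives alpha 0.05, power 80%, effect size 0.25, repeated measures ANOVA, 45 participants, 20% dropout and a target of 60 (12 per group). I took 0.25 as Cohen's f and the test as the group-by-time interaction, with k = 5 groups and m = 3 times. The correlation and sphericity values are not stated, so I assumed rho = 0.5 and epsilon = 1.

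- Noncentrality: f² × N × m / (1 − rho) = 0.0625 × 45 × 3 / 0.5 = 16.9.
- Degrees of freedom: (5 − 1)(3 − 1) = 8 and (45 − 5)(3 − 1) = 80.
- Power is 0.810, and 45 is the smallest multiple of 5 that reaches 80%. With rho = 0.3 the required N would be 65, and with rho = 0.7 it would be 30.
- Dropout: 45 / 0.8 = 56.25, so 57, rounded up to 60 for equal arms.

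The stated figures reproduce under these assumptions, and this point does not dispute them.

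**2. Effect on power.** On the same assumptions, power is 0.930 at N = 60, 0.925 at 59, 0.919 at 58 and 0.913 at 57. Losing a few patients to this rule does not threaten power.

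**3. Effect on an arm's mean.** Suppose k of 12 patients are lost and their unseen outcome is g SD worse than that of the patients who stay. The full-arm mean is then the completer mean minus (k/12) × g, so the completer mean is too favourable by (k/12) × g. The gap g is an assumption, taken as 0.5 to 1.0 SD.

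| Patients lost from one arm | g = 0.5 SD | g = 1.0 SD |
|---|---|---|
| 1 | 0.5/12 = 0.042 SD | 1.0/12 = 0.083 SD |
| 2 | 2 × 0.5/12 = 0.083 SD | 2 × 1.0/12 = 0.167 SD |

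**4. Effect on precision.** The ratio of standard errors for a pairwise contrast, with the other arm complete, is sqrt[(1/(12 − k) + 1/12) / (2/12)].

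- k = 1: sqrt(0.1742/0.1667) = 1.02.
- k = 2: sqrt(0.1833/0.1667) = 1.05.

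**5. How often.** The protocol gives no event rates. With an assumed serious-event risk of 1%, 2% or 5% over four weeks, 60 × risk gives 0.6, 1.2 or 3 patients in the whole trial. Per arm, 1% to 5% of 12 is 0.12 to 0.6 patients. The expected shift in an arm's mean is risk × g, from 0.01 × 0.5 = 0.005 SD to 0.05 × 1.0 = 0.05 SD.

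**6. Fit with the named analyses.** A mixed model keeps a withdrawn patient's T0 value and any T1 value, in the randomised arm. A repeated measures ANOVA on complete cases drops anyone missing T1 or T2. The protocol names both models and does not fix which applies to the primary outcome, so the cost of the rule depends on a choice still open.

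**The case against.** The strongest objection is that the data loss is inferred. The article says the participant leaves the trial; it does not say in so many words that assessments stop, and a fuller protocol might arrange follow-up. The literal point is right. But the article states a rule on this very question, and the ordinary meaning of leaving a trial is that its visits end.

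Second, the clash with the analysis is limited. Patients keep their randomised arm, the mixed model is named first, the likelihood ratio test of treatment and time-by-treatment terms fits it, and complete-case analysis is nowhere specified. This stands as far as it goes: there is no formal contradiction of intention-to-treat. It does not restore the unseen values.

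Third, the serious event itself is still recorded in the case report form and reported, and the questionnaire completed after each tDCS session would end once stimulation stops in any case. That is also correct. The safety loss is confined to the scheduled Adverse Reaction Scale at T1 and T2.

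Fourth, the size is not anchored in data. The protocol regards risk as minimal, two serious events in one arm would be a rate of 2/12 = 17%, and similar losses in both arms would partly cancel. Some patients with a serious event would also be too ill for a ten-test battery, so only part of the loss is avoidable. These points hold and limit the importance of the concern, but they do not justify keeping the rule when the alternative uses visits already scheduled.

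**Conclusion.** The concern holds. As written, a serious adverse event ends the participant's whole trial participation, and the remaining MCCB and Adverse Reaction Scale assessments go with it. The rule undermines the intention-to-treat analysis and the safety follow-up without formally contradicting either commitment.

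The effect is probably small: 0.04 to 0.08 SD on an arm's completer mean per patient lost, with a 2% to 5% increase in a contrast's standard error for one or two losses. These figures rest on an assumed outcome gap of 0.5 to 1.0 SD and an unknown number of events. The issue is possible bias and lost safety information, not power. Confidence is moderate, because the loss follows from the ordinary meaning of the text and not from an explicit statement that visits cease. The change should be made because the loss cannot be repaired afterwards and the remedy is cheap.

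**What to change.** - **Harms:** replace withdrawal from the trial with stopping that participant's intervention as clinically needed. The clinical decision and the report to the ethics committee stay as they are.
- **Harms or Outcomes:** state that the participant is still invited to the scheduled T1 and T2 assessments, including the MCCB and the Adverse Reaction Scale, unless consent is withdrawn, and is analysed in the randomised group.
- **Eligibility criteria:** make the list refer to discontinuing the participant's intervention. Its present wording literally stops the study. Keep withdrawal from the study for the third ground only, unwillingness to continue.

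The cost is a wording change through the route in *Protocol amendments*, which is needed because recruitment began in December 2024. No visits are added. The downside is a few assessments in patients no longer being treated, some of whom may be too unwell to complete them.

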### Auditing

The Principal Investigator will checked the CRFs and completed pro formas on a weekly basis. Research records in both paper and digital forms will be checked every two weeks for accuracy, and any discrepancies will be noted, discussed, and corrected.

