### Blinding

All participants and the psychiatrists conducting the assessments will remain blinded during the study. Regarding the implementation of blinding procedures, we have established the following considerations and measures. The specific group assignments of patients will be disclosed exclusively to the principal investigator. Furthermore, five distinct groups will be engaged to execute the treatment, with stringent restrictions in place to prevent inter-team communication concerning the details of their respective treatment. Each group will be informed solely of its own treatment plan and will remain unaware of both the specific group assignments and the plans of the other teams. During the experiment, the principal investigator will provide each group with the designated measures. Subsequently, each team will implement the experimental treatments on their respective patient cohorts. Patients remain blinded to the sequence allocation and are instructed to refrain from discussing group assignments, the treatments received, questionnaire completion, or any other elements of the experimental protocol among themselves. During the outcome measurement phase, personnel tasked with data collection and analysis are also blinded to the group assignments and specific measures. Next, the principal investigator will perform two unblinding procedures, one prior to and one following the data analysis. The initial unblinding will occur post data-lock, categorizing the data into Groups 1-5 without disclosing the actual alignment with Groups 1, 2, 3, 4, and 5, or their true group assignments. The second unblinding will be conducted after the completion of data analysis, elucidating the specific group identities corresponding to Groups 1, 2, 3, 4, and 5.

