### Date management

Cognitive function and the severity of psychotic symptoms will be assessed by two clinical psychiatrists who remain blinded to the group allocation. All demographic data and scale-related information will be recorded in electronic CRFs and stored on a designated website. Access to these securely stored CRFs will be restricted to the project leader and the principal investigator. To ensure patient confidentiality, pseudonymization will be employed by substituting real patient names with unique identification numbers during data entry. Although the trial does not incorporate a data monitoring committee, oversight of the subject group is entrusted to a designated individual. Patient adherence to tDCS or MT sessions will be facilitated through notifications sent via WeChat.

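### The principal investigator, who holds all assignments, also checks the outcome CRFs weekly before data lock, which undercuts the purpose of blinding the data handlers

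*Protocol article*

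**What the plan says.** Three sections of the protocol article bear on this point.

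- **Blinding.** On who knows the arms: "The specific group assignments of patients will be disclosed exclusively to the principal investigator". During treatment, "the principal investigator will provide each group with the designated measures", and at the end "the principal investigator will perform two unblinding procedures, one prior to and one following the data analysis". On data handling, "personnel tasked with data collection and analysis are also blinded to the group assignments and specific measures". On timing, "The initial unblinding will occur post data-lock", and that step releases only coded groups; true identities follow after the analysis.
- **Date management.** Demographic and scale data go into electronic CRFs under pseudonymous numbers. "Access to these securely stored CRFs will be restricted to the project leader and the principal investigator". Cognition and psychotic symptoms are assessed by two psychiatrists blinded to allocation.
- **Auditing.** "The Principal Investigator will checked the CRFs and completed pro formas on a weekly basis". A second sentence has paper and digital records checked for accuracy every two weeks, and "any discrepancies will be noted, discussed, and corrected". That sentence names nobody as the checker or the corrector.

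The Randomization section describes an independent statistician with no other part in the study, who randomizes the patients. The Data monitoring section says that no data monitoring committee was required.

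**The concern.** Releasing group codes only after lock, and identities only after analysis, is meant to settle the outcome data before anyone who works on them can connect a record with an arm. The role assignments work against that. The one study role told every assignment reviews the outcome records each week while they can still be changed.

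What is at stake is the handling of scores after they have been rated. A person who knows the arm might look harder at some records than at others, or might have a say in which discrepancies are raised and how they are settled. Nobody need intend this for it to matter. Scales that rest on judgement are the most exposed, since a queried rating has more room to move than a test score. With 12 patients per arm, a small number of altered records could be noticeable, and no later analysis can show that the checks were neutral. The trial describes itself as double-blind, so it should be able to say that its outcome records were also checked and corrected without knowledge of the arm.

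**Working it through.** No arithmetic applies: the point depends on who holds which information and when. The protocol states no figure that could be reproduced. The check sets the role assignments side by side.

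| Question | What the protocol article provides | Section |
|---|---|---|
| Which study role is told all assignments? | The principal investigator, exclusively | Blinding |
| Does that role use them while the trial runs? | Yes, in giving each treatment team its measures | Blinding |
| Where are the scale scores kept? | In electronic CRFs | Date management |
| Who can open the CRFs? | The project leader and the principal investigator | Date management |
| Who checks the CRFs weekly? | The principal investigator | Auditing |
| Who performs the two-weekly check and correction? | Not named | Auditing |
| When are coded groups first released? | After data lock | Blinding |
| Who gives the cognitive and symptom ratings? | Two blinded psychiatrists | Date management |

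1. The first two rows make the principal investigator aware of every arm throughout treatment.
2. The next three rows give that role continuing sight of the scale data. The weekly check takes place during the trial, so it precedes lock.
3. Pseudonymization hides the patient's name. It does not hide the arm from the person who was given the assignments.
4. Correction of records belongs to the two-weekly check. The principal investigator's part in it is neither stated nor excluded. For the electronic CRFs, only two roles have access, and the principal investigator is one of them.
5. The sentence blinding data collection and analysis personnel does not list the principal investigator. Checking CRFs is strictly neither collecting nor analysing data, so the sentences can stand together as written. The tension is between the function given to the principal investigator and the purpose of the blinding scheme.
6. The primary outcome, the MCCB, is a battery of performance tests. PANSS, BPRS and CGI are secondary and depend on a rater's judgement. Any effect of unblinded checking would therefore be expected mainly on the secondary scales.

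As the roles are written, before lock an arm-aware person reviews outcome records, in an auditing procedure that includes correction by an unnamed actor.

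**The case against.** The strongest reply is that the protocol is open about its one unblinded role and blinds everyone who produces or analyses the data. The psychiatrists rate blind, the analysts receive coded groups after lock, and identities are opened only after analysis. The weekly check can be read as routine oversight, and the two-weekly check as accuracy checking of paper against digital records. Nothing says that scores are re-rated. Audit trails, query rules and field-level permissions commonly sit in a full protocol or data management plan, and this is a condensed article.

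Much of this stands, and it rules out several stronger readings that a reader might infer:

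- **That the protocol contradicts itself.** It does not do so literally, because the principal investigator is not named among the blinded personnel.
- **That the principal investigator corrects the records.** The correcting check has no named actor.
- **That the principal investigator queries the blinded raters, or that discussion of discrepancies reveals the arm to them.** The Auditing section does not say who takes part in the discussion.
- **That nobody else has ever held the list.** The independent statistician who randomizes will have held it too, although no CRF access is stated for that role.
- **That the bias can be sized.** One record shifted by 1 SD moves the mean of a 12-patient arm by 1/12 = 0.083 SD, and three such shifts that all favour the same side move a contrast by 3/12 = 0.25 SD. But the number, size and direction of corrections are all assumed here. The documents give none of them.

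The appeal to a fuller document does not remove the point. It does not rest on a missing audit trail. It rests on three assignments that the article itself makes to one role: code holder, CRF access and weekly checker.

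**Conclusion.** The point holds as a weakness in how duties are divided. The principal investigator holds all assignments, has one of two CRF accesses and checks the CRFs weekly before lock. That undercuts the reason for blinding data handlers and delaying the release of codes, and it leaves a possible route for arm knowledge to affect outcome records. The exposure falls mainly on PANSS, BPRS and CGI, and less on the MCCB.

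No bias is shown, and its size cannot be estimated from the documents. The conclusion assumes that the CRFs open to the principal investigator include the outcome fields, which is what the Date management section indicates, and that the project leader and the principal investigator are different people, as their separate listing suggests. A reader might go further and infer that the outcome data will not be handled blind at all. The blinded raters and the coded release after lock do not support that. Because the remedy costs little and analysis cannot supply it afterwards, the change is worth making promptly; recruitment began in December 2024.

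**What to change.** **Preferred change.** In Date management and Auditing, assign all checks, queries and corrections of outcome data before lock to the project leader, who is to be kept blinded to allocation. The Blinding section already withholds the assignments from that role. Name the project leader as the actor in the two-weekly check, require each change to an outcome value to be logged, and withhold outcome CRFs from the principal investigator until data lock. The Harms section records adverse events from each tDCS session in the CRF, and those entries would show who receives stimulation sessions. The blinded checker should therefore work from the outcome pages only.

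**Alternative.** Let the independent statistician described under Randomization keep the allocation list and perform both unblindings, so that the principal investigator stays blinded and can go on checking CRFs. The task of giving the treatment teams their measures would then also have to leave the principal investigator.

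**Cost.** The preferred change shifts duties between existing roles and amends the wording of two sections, with no added staff. The alternative gives the statistician a continuing task in a study from which that person was otherwise to be separate. Neither touches treatment, eligibility, sample size or the assessment schedule.
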